### Description of intervention and control arms

Control practices: In GP practices allocated to the control arm patients will continue to be managed according to usual GP-led care. This normally consists of a patient consulting their GP and receiving advice and treatment (often medication but we expect around 20–25 % to be referred to physiotherapy, or for a diagnostic test or other treatment service). For some patients, it may mean being triaged by a practice nurse and managed with advice and/or referral to physiotherapy or other services. Usual GP-led care therefore includes all of these pathways in participating GP practices but will not include the offer of direct access to physiotherapy. No additional information on physiotherapy services will be disseminated by the research team to GP practices delivering usual care. Regular contact with, and feedback to, the control practices through CRN staff, a GP research facilitator and from the PI and study team will help ensure smooth trial operationalisation.

Intervention practices: In practices allocated to the intervention arm patients will continue to be able to access care via usual GP-led care pathways (as described above) in addition to direct access to physiotherapy for musculoskeletal patients. Direct access will allow adults with musculoskeletal problems to refer themselves to the physiotherapy service. Those opting for direct access to physiotherapy will complete a self-referral form, which will be available at their GP practice or, where possible, online. The self-referral form will include questions about ‘red flag’ symptoms, indicative of suspected serious pathology that would require urgent medical investigation, with advice to patients to contact their GP if one or more of these symptoms are present. Submitted self-referral forms will be reviewed by a senior physiotherapist who will identify, based on existing physiotherapy service criteria, whether the referral is appropriate and whether classed as urgent or routine. Urgent cases will be offered the next available appointment whereas routine cases will join all other routine patients on a waiting list for the physiotherapy service and be seen in order of receipt of referral. In cases where the referral is considered inappropriate for physiotherapy management, the patient will be contacted by the physiotherapy service and signposted to the most appropriate practitioner or service. Direct access to physiotherapy will be actively marketed in the intervention practices to ensure that all registered patients are aware of this option [30]. This will start eight weeks prior to participant recruitment to the research evaluation and continue until patient recruitment to the trial has finished. Marketing will include communications with practice staff (clinical and administrative teams), practice posters, rolling presentations in practice waiting areas (where possible), patient flyers and self-referral forms in practices. In order to best ensure that all adults in the practice become aware of the availability of direct access, an information letter and direct access flyer will be mailed to all registered adult patients at each intervention practice. A phased approach to the marketing of the new service is planned, over 8 weeks, so that demand for physiotherapy through direct access can be monitored. The posters, flyers and forms will clearly explain how patients can directly access the service. The physiotherapy administrator will input patients’ data into the trial registration database and be responsible for arranging face-to-face physiotherapy appointments at convenient times and dates following prioritisation of the referrals by senior physiotherapists in the service. Even with the offer of direct access, we anticipate that many patients will opt to consult their GP as usual. Therefore, in the intervention practices, patients may consult their practice and be referred to physiotherapy, either by written referral or be recommended to access physiotherapy by GPs or nurse practitioners (GP or nurse recommended self-referral) or choose to directly access physiotherapy without contacting their GP practice (true self-referral). Each patient’s pathway will be recorded.

### Support for physiotherapists providing the direct access service

Although physiotherapists are autonomous practitioners on qualification, additional education and development needs of physiotherapists have been identified as part of the work-up of the pilot trial and a training programme is planned to address these. The brief training programme will include the following content: prevalence and identification of red flags, serious pathology and medical masqueraders, review of common over-the-counter and prescribed medications for musculoskeletal pain patients, the provision of occupational/work advice to patients and information about the practicalities of the trial, including delivery of the trial protocols and identification of any serious pathologies or serious adverse events. Continuing support of physiotherapists delivering the direct access service will take the form of a mentoring programme provided by the lead musculoskeletal physiotherapist in the team and another senior physiotherapist who has experience of providing direct access services. The physiotherapy service leads will also agree pathways for patients using direct access with suspected serious pathology who are in need of medical attention, or who may require a fit note or a prescription from their GP. Approximately 18 physiotherapists will participate in the training programme, half of whom will initially provide the new direct access physiotherapy service and the remainder will be able to provide cover as needed throughout the duration of the trial, for example for holiday periods.

### Outcome measures

Process outcomes: Process outcomes will determine if a future main trial is possible and desirable. Anonymised process outcome data will be collected from GP records and physiotherapy administration databases and self-referral forms. Health service process outcomes include the proportion of patients not referred to physiotherapy services, those referred to physiotherapy and the number of patients directly accessing physiotherapy in the intervention practices, proportion of ‘recommended self-referral’ and ‘true self-referral’ in the direct access pathway, waiting times for treatment (time from logging of referral to first physiotherapy appointment), number of GP and NHS physiotherapy consultations for musculoskeletal problems and non-attended physiotherapy appointments (DNA rates). Research process outcomes include estimation of recruitment rates, exploration of evidence of selection bias and follow-up rates at each time-point with differences in the control and intervention practices explored to identify sources of bias. A summary of the process measures is shown in Table 1.

**Table 1 Tab1:** STEMS pilot trial process measures

Engagement of GP practices and PT services
Physiotherapy site recruitment rate to participate in STEMS study
GP Practice recruitment rate to participate in STEMS study
Research evaluation
Recruitment rate to the research evaluation—all adults with musculoskeletal conditions
Recruitment rate to the research evaluation—‘true self-referral’^a^ patients
Recruitment rate to the research evaluation—‘recommended self-referral’^b^ patients
Retention rates to research evaluation at 2, 6 and 12 months follow-up
GP practice characteristics
Number of GPs and nurse practitioners per practice
Number of patients and number of adults registered at practice
GP consultation rates for adults with musculoskeletal conditions (before and during study)
Physiotherapy team characteristics
Number of physiotherapists working in the physiotherapy service (in total and STEMS trained)
Seniority of physiotherapists in the physiotherapy service (in total and STEMS trained)
Physiotherapy service
Physiotherapy service GP referral rate (before and during study)
Physiotherapy service ‘true self-referral’^a^ rate
Physiotherapy service ‘recommended self-referral’^b^ rate
Non-attendance rates at physiotherapy site for GP referrals (before and during study) and for self-referrals during study
Number of physiotherapy consultations for GP referrals, ‘true self-referral’ and ‘recommended self-referral’ patients in the intervention practices
Number of self-referring patients deemed unsuitable at each stage in the direct access pathway
Onward referral rate from physiotherapy (to GP, other services) for GP referrals, ‘true self-referral’ and ‘recommended self-referral’
Physiotherapy waiting time (month-by-month) from 12 months prior to introduction of direct access to end of study
Number of patient complaints about direct access at physiotherapy site
Monitoring of safety
Number of cases of missed serious pathology in patients directly accessing physiotherapy
Number of adverse events in GP-referred, ‘true self-referral’ ‘recommended self-referral’

^a^Those who are prompted by their GP or practice nurse to access physiotherapy care

^b^Those who directly access physiotherapy care without prompting by their GP or practice nurse

Clinical outcomes: Data collection will include the collection of clinical and cost data through patient self-report questionnaires at baseline and 2, 6 and 12 months follow-up. The primary clinical outcome is physical health measured using the SF36v2 Physical Component Summary. A summary of the clinical outcomes and other measures included in each questionnaire is shown in Table 2.

**Table 2 Tab2:** STEMS pilot trial questionnaire measures

Domains	Description				
		Baseline	2 months	6 months	12 months
Primary outcome measure					
Physical function	SF36v2 physical component summary http://www.sf-36.org/	✓	✓	✓	✓
Secondary outcome measures					
Overall change in condition	Global assessment of change since baseline—single question	✘	✓	✓	✓
Mental health	SF36v2 mental component summary http://www.sf-36.org/	✓	✓	✓	✓
Quality of life	EuroQol EQ-5D-5 L www.euroqol.org	✓	✓	✓	✓
Self-efficacy	Pain self-efficacy questionnaire (PSEQ) [31]	✓	✓	✓	✓
Understanding of condition	General practice assessment questionnaire enablement subscale [32]	✓	✓	✓	✘
Experience of consultations	General practice assessment questionnaire communication [32]	✓	✓	✓	✘
Accessibility of services	Single question	✘	✓	✓	✘
Satisfaction with services	Single question	✘	✓	✓	✘
Baseline measures					
Demographics	Gender, date of birth, ethnicity, education, health literacy, employment status, socio-economic status (recent paid job title, housing)	✓	✘	✘	✘
Baseline risk of persistent problems	STarT Musc tool (draft tool developed at Keele University to identify patients’ risk of persistent pain and disability)	✓	✘	✘	✘
Pain location	Body manikin	✓	✘	✘	✘
Pain duration	Single question about duration of pain	✓	✘	✘	✘
Comorbidities	Single question	✓	✘	✘	✘
Economic outcomes					
Further health care utilisation	Consultations, investigations, procedures, admissions, over-the-counter medications	✘	✘	✓	✓
Work absence	Single question	✓	✓	✓	✓
Presenteeism	Single work performance question	✓	✓	✓	✓
Willingness to pay	Three willingness to pay questions	✘	✘	✘	✓

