### Setting and clusters

The setting is primary care in England for adults with musculoskeletal problems (GP practices and linked NHS physiotherapy services). GP practices are the unit of randomisation, and thus, patients follow the care pathways to which the practice is randomised. In this pilot, RCT practices will be stratified only on practice size, but in a main trial, practices would also ideally be stratified by index of deprivation. Randomisation of GP practices will be undertaken by an independent statistician. GP practices will be randomised to one of two arms, either to continue with usual GP-led primary care for musculoskeletal patients with the addition of the offer of a self-referral physiotherapy pathway (intervention group) or to continue with usual GP-led primary care alone (usual care control group). Practices will be randomised according to a computer-generated random numbers stratified by the practice size (small or large) in the ratio 1:1. In a main study, we would plan to further stratify by practice setting and area level deprivation (through minimisation) in order to ensure balance in key practice characteristics in each arm of the trial.

GP practices are eligible to take part if they meet the following criteria: they are within the Vale Royal Clinical Commissioning Group area of Cheshire and the Clinical Research Network (CRN); they are a group practice, currently referring musculoskeletal patients to NHS physiotherapy services; they do not currently offer direct access to physiotherapy; and they are willing to test direct access. The balance between scientific considerations and the need for consent is a known issue for cluster trials [27]. Informed consent for practices to participate will be provided by the senior GP partner in each practice acting as ‘guardian’ for patients in their care. Patients will follow the care to which their practice is randomised with identical patient information for both arms providing general information about the study, explaining that their local musculoskeletal services are being evaluated using patient self-reported clinical outcomes and medical record review. Individual patients will therefore be able to opt out of data collection.

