### Adverse events

The occurrence of adverse events from all interventions will be monitored and assessed using case report forms, contact with the trial coordinator, physiotherapist report, and follow-up questionnaires. However, as the intervention is the introduction of a direct access pathway and the treatments received will be the same as in usual clinical practice, adverse events are unlikely. Physiotherapists and GPs will report any serious adverse event (SAE) experienced by a trial participant immediately to the trial chief investigator that may possibly be related to either the interventions or the trial procedures. The chief investigator will assess whether the event was related to or resulted from any of the STEMS study trial interventions or procedures. Any SAE considered to be related to the trial procedures or interventions will be reported to the main Research Ethics Committee by the chief investigator within 15 days of her becoming aware of the event. In addition, all such events will be reported to the trial sponsor, Trial Steering Committee and Data Monitoring Committee.

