#### Feasibility of direct access

An audit of the feasibility of offering direct access will be conducted using anonymised data. This will include reporting the number of participants who are referred to physiotherapy by their GP, those who are ‘recommended self-referrals’ (prompted by their GP or practice nurse to refer) and those who are ‘true self-referrals’ and the waiting time to the first physiotherapy appointment. Figures will be presented month-by-month for patients using direct access as well as the overall totals. The proportion of patients directly accessing care (true and recommended self-referrals) compared to all referrals received at the physiotherapy site will be calculated to check the success of marketing the direct access service. The aim is to ensure that a minimum of 20 % of the total physiotherapy caseload during the pilot trial, from practices randomised to the intervention arm, is through direct access. In order to assess the feasibility of establishing a direct access service that can respond to demand, descriptive measures of the total number of referrals received from participating practices and staffing levels in the participating physiotherapy department will be used to establish how the physiotherapy service responds to demand through waiting time for first physiotherapy appointment. The source by which patients, who access care directly, become aware of the direct access service will be presented and compared in order to establish which methods (GP advised, poster, individual mailing, heard from a friend and other methods) are most successful in marketing the service.

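### The stated adverse-event measure counts events by referral pathway, not by randomised arm, and has no category for participants not referred to physiotherapy

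*Protocol article*

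**What the plan says.** All references are to the protocol article.

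- **Outcome measures, Table 1, Monitoring of safety.** The adverse-event row opens "Number of adverse events in GP-referred" and reads in full "Number of adverse events in GP-referred, ‘true self-referral’ ‘recommended self-referral". The only other safety row counts missed serious pathology in patients who access physiotherapy directly, and the section Safety of direct access to physiotherapy confines that count to such participants.
- **Adverse events.** Collection is wider than the table: "The occurrence of adverse events from all interventions will be monitored and assessed using case report forms", together with contact with the trial coordinator, physiotherapist reports and follow-up questionnaires. Both physiotherapists and GPs are to report possibly related serious adverse events (SAEs) in any trial participant.
- **Setting and clusters.** The randomised unit is the GP practice: "Practices will be randomised according to a computer-generated random numbers stratified by the practice size (small or large) in the ratio 1:1".
- **Description of intervention and control arms.** For usual care, "we expect around 20–25 % to be referred to physiotherapy, or for a diagnostic test or other treatment service". For the intervention practices, "Even with the offer of direct access, we anticipate that many patients will opt to consult their GP as usual".
- **Feasibility of direct access.** "The aim is to ensure that a minimum of 20 % of the total physiotherapy caseload during the pilot trial" from the intervention practices comes through direct access.

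Recruitment, follow-up, baseline characteristics, clinical outcomes and missing outcome data are each to be compared between the arms in their own Analysis subsections. No section states a count of adverse events by arm.

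**The concern.** The future trial's question is whether adding the offer of direct access differs from usual GP-led care alone. The groups that answer it are the randomised practices' patients. Referral pathway is something patients and GPs choose later, partly in response to the allocation, so a count by pathway does not contrast those groups.

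Pathway is also related to risk, on the article's own account. It accepts that people who go directly to physiotherapy may differ from those who see a GP. It expects written GP referral to suit frail older people and complex cases. Its self-referral form directs people with red-flag symptoms to their GP, and a senior physiotherapist screens the submitted forms. A lower event count in the self-referral rows could therefore reflect who was routed there.

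Events in people managed by the GP without physiotherapy, who are most of the control arm on the article's figures, would not appear in the measure at all. Process measures are meant to help decide whether a main trial is feasible and desirable. A pilot that summarises harm only in this way would not have tried out the safety summary a main trial needs.

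**Working it through.** **1. Which arm can fill each row**

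| Table 1 category | Control arm | Intervention arm |
|---|---|---|
| GP-referred | yes | yes |
| True self-referral | no | yes |
| Recommended self-referral | no | yes |
| Not referred to physiotherapy | no category | no category |

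Only the first row can contain control participants, and as written it is not split by arm. Another Table 1 row, on the number of physiotherapy consultations by pathway, is expressly limited to intervention practices. The adverse-event row carries no such limit. If one was intended, the control arm would have no adverse-event count whatever.

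**2. The article's own recruitment figure (Sample size)**

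- 5000 × 25% = 1250 consulters per year; 1250 / 12 = 104.2, which the article rounds to 100 per month.
- 100 × 80% eligible = 80; 80 × 50% responding = 40 per practice per month.
- 40 × 4 practices × 6 months = 960; 960 × 80% = 768 followed up.

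Both stated figures, 960 and 768, reproduce exactly.

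**3. Control participants in no row**

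Assume equal arms: 960 / 2 = 480. In no row = 480 × (1 − proportion referred to physiotherapy).

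- At 25% referred: 480 × 0.75 = 360.
- At 20% referred: 480 × 0.80 = 384.

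The 20–25% may also cover diagnostic tests and other services. If so, the physiotherapy share is smaller and more control participants fall outside the table.

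**4. Both arms together (illustration; the article gives no intervention-arm figure)**

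Assume GP referral in the intervention arm stays at p = 20–25% of participants and direct access makes up a share s of that arm's physiotherapy caseload. Physiotherapy use is then u = p / (1 − s).

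| s | p | u | Intervention, no row | Control, no row | Total of 960 |
|---|---|---|---|---|---|
| 20% | 20% | 25% | 360 | 384 | 744 (77.5%) |
| 20% | 25% | 31.25% | 330 | 360 | 690 (71.9%) |
| 50% | 20% | 40% | 288 | 384 | 672 (70%) |
| 50% | 25% | 50% | 240 | 360 | 600 (62.5%) |

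For fewer than half of all participants to be in no row, 480 × (1 − u) plus the control figure must be below 480, so u must exceed 360/480 = 75% (p = 25%) or 384/480 = 80% (p = 20%). That sits badly with the article's expectation that many intervention patients will still consult their GP as usual.

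**The case against.** The strongest reply is that Table 1 is a summary of process measures, and its row lists a count without prescribing a comparison. Nothing says adverse events will be reported by pathway alone; where the authors meant to restrict a safety report, for missed pathology, they said so. A table by arm could sit in the full protocol or the statistical analysis plan, neither of which is shown. Most of the physiotherapy-service rows use the same pathway split, and asking whether events occur in the new pathway is a proper pilot question. Adverse events are described as unlikely, analysis is mainly descriptive, and only four practices are randomised.

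Much of this stands. It limits the weight of the point and justifies keeping the pathway breakdown. It does not remove the point, because the article does more than stay silent on grouping: it names one, and the one it names omits most of the control arm. A by-arm table elsewhere would still leave this row needing correction.

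Two stronger readings are tempting and should not be adopted:

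- **That the trial cannot compare the arms on harm.** A reader might infer this from Table 1. However, the Adverse events section monitors events from all interventions and takes SAE reports for any participant, and a participant's practice fixes the arm. If collection runs as described, a count by arm can be made.
- **That the self-referral rows will hold only a few dozen people.** Taking 20–28% of a caseload of 96–120 (20–25% of 480) gives 19–34. But 20% is a minimum target, 28% is the top of a range from a Dutch evaluation cited in the Background, and the sum holds the caseload fixed although self-referral may add to it. At s = 50% in the working, self-referrers would number 96–120. Nor are raw counts beyond repair, since the numbers in each pathway are to be reported and can serve as denominators.

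**Conclusion.** The point holds for the measure as stated. It groups participants by something formed after randomisation, two of its three categories are confined to one arm, the third mixes the arms, and participants not referred to physiotherapy have no place in it. On the article's referral figure, about 360–384 of 480 control participants (75–80%) would be in no row.

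That figure assumes equal arms, that recruited participants are referred at the rate expected of usual-care patients, and that GP-referred means referred to physiotherapy, as the Feasibility of direct access section describes it. Referral later in the 12 months would lower the number. The statement that most participants across both arms are in no row needs the further assumptions about intervention-arm uptake shown in the working; it survives all the cases tried there.

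This is a defect in the safety summary, not in data collection. It is worth correcting, but with few events expected and two practices per arm if the 1:1 allocation is met, any comparison will be descriptive.

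**What to change.** In Table 1, under Monitoring of safety:

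1. State adverse events and SAEs by randomised arm: the number of participants with at least one event and the percentage, with all recruited participants in that arm as denominator. Present these descriptively. Do not attach a confidence interval that treats patients as independent, since with two practices per arm it would be too narrow.
2. Keep the pathway breakdown as a secondary description. Give the denominator for each category and add a row for participants not referred to physiotherapy.

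No new data are needed: arm follows from practice, the article says each intervention patient's pathway is recorded, the proportion not referred is already a process outcome, and events are to be monitored for all interventions. The cost is a short edit to Table 1 and one further descriptive table. The drawback is that this table will probably contain few events and, with four clusters, cannot support a firm conclusion about relative safety; the text should say so.
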